### 2.2. Participants

Participants for the SENSe CONNECT study include both therapists and stroke survivors.

Therapists: Inclusion criteria—Qualified occupational therapist or physiotherapist; current registration to practice; and willing to participate in the upskilling in SENSe therapy, undertake evaluation, and actively participate in mentoring and treatment fidelity activities to develop competency to deliver SENSe therapy. There are no additional exclusion criteria for the participants who are therapists. Replacement therapists will be recruited as needed. As a pragmatic implementation trial, restrictions will not be imposed on therapist participants’ experience or number of stroke survivors treated. However, demographic information for all therapist participants will be collected to ascertain relationships between stroke survivor outcomes and therapist characteristics.

Stroke survivors: People with stroke living in the community and presenting with new or chronic somatosensory impairment will be recruited. Stroke survivors may be referred via partner organizations, neurologists, rehabilitation physicians, general practitioners, other organizations, or self-referral. Inclusion criteria: A clinical diagnosis of stroke (including infarct or hemorrhage, people with a second stroke, no restriction on time since stroke); impaired touch sensation, limb position sense, and/or tactile object recognition of the upper limb, identified clinically and with screening tests; medically stable; able to give informed consent; able to comprehend simple instructions; willing to commit time to participate in the SENSe therapy program; and living in the community. Key exclusion criteria: Sensory impairment not due to stroke; severe unilateral spatial neglect (measured via line bisection and shape cancellation task); prior history of other central nervous system dysfunction with an unstable or progressive prognosis; severe to moderate cognitive impairment (i.e., not able to comprehend simple instructions or sustain attention needed to participate in treatment); not able to give informed consent; physical limitations that prevent participation in therapy tasks (e.g., contracture of the hand, or unhealed wounds); and unable to participate in a clinical appointment lasting 30 min. Thus, the design tests effectiveness with relatively unselected survivors of stroke in the community.

### 2.3. Setting

Specialist SENSe therapy centers will be based at four metropolitan sites in Australia, each having a link with a health setting and an academic or research organization. Sites are Austin Health (link with Florey Institute of Neuroscience and Mental Health and La Trobe University) and Alfred Health (link with Monash University) in Melbourne, Victoria; John Hunter Hospital (link with University of Newcastle) in Newcastle, NSW; and UniSA Health (link with University of South Australia) in Adelaide, SA.

### 2.4. Outcomes

Access to evidence-based sensory rehabilitation: The primary outcome is the number of complete deliveries of SENSe therapy at the SENSe therapy center by therapists credentialled in SENSe therapy. A delivery will be counted as complete if it meets the criterion of at least 7 sessions delivered with a stroke survivor.

Stroke survivors: The primary outcome is change in arm somatosensory function, pre–post SENSe therapy, across three somatosensory domains, measured using standardized, quantitative somatosensory measures and a normalized summary impairment index calibrated to normed age-matched performance [34,45]. The index will be derived from scores on the Tactile Discrimination Test [46], Wrist Position Sense Test [47], and functional Tactile Object Recognition Test [48]. Each of these quantitative measures assesses the person’s ability to discriminate different somatosensations; i.e., texture discrimination, wrist joint proprioception, and haptic object recognition of the upper limb. Comparable ranges of impairment from just noticeable to extreme impairment defined for each measure enable the normalization of the three test scales for comparison in clinical and research settings [45].

The following secondary outcomes will also be assessed: client-rated performance and satisfaction of valued activities, using the Canadian Occupational Performance Measure (COPM) [49] and clinician-rated performance on the same valued activities using the Performance Quality Rating Scale for Somatosensation after Stroke [50]; arm use, using Motor Activity Log-14 [51]; and health-related quality of life, using the Assessment of Quality of Life (AQoL-6D) [52]. See Table 1 for the schedule of study outcomes.

Therapists: Treatment fidelity is a primary outcome for therapists and will be assessed as the ability to deliver SENSe therapy with high fidelity measured with a criterion-based checklist (comprising 29 components core to the delivery of SENSe therapy; 80% fidelity) and customized documentation audit checklist [43]. Fidelity will be assessed by an independent person, using a document audit, for each therapist after delivery of each 6-week program of SENSe therapy. In addition, a sample of treatment sessions (early, middle, and late in the sequence of 10 sessions for the stroke participant) will be observed and rated by an independent person using a session-based treatment fidelity checklist. Therapist participants will also be assessed for change in practice behaviors related to SENSe therapy (secondary outcome), specifically change in knowledge, skill, and confidence levels. These outcomes will be assessed using pre–post implementation questionnaires [12] adapted for the SENSe CONNECT study. The pre-questionnaire will be completed prior to upskilling, credentialing, and first delivery of SENSe therapy. The post-implementation questionnaire will be completed after delivery of therapy to the 12th stroke survivor treated, or following the last scheduled delivery of therapy, for that therapist.

Therapist experience effect: Therapist experience will be measured according to the number of completed deliveries of the SENSe therapy program, with delivery of 7 or more sessions per stroke survivor the criterion for a completed delivery. Each therapist is anticipated to deliver SENSe therapy to 6 to 12 survivors of stroke.

Resource utilization and therapy costs: Resources used by survivors of stroke will be collected at all assessment occasions for the usual care wait list and intervention periods using a patient/carer survey. Resources will be assigned prices to convert these into costs using contemporaneous Australian reference sources. Costs will be inflated/deflated for a common reference year (e.g., 2022) using the Total Health Price Index [53], as required. Program level costs of intervention delivery: SENSe therapy costs will include the cost of upskilling therapists, equipment, and delivering the intervention according to the model of care established, as well as determining the cost of usual care. The type and quantity of each resource used will be collected in natural units, e.g., number of sessions and time taken to train therapists.

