#### 2.1.2. Specialist SENSe Therapy Centers and SENSe CONNECT Protocol

Four specialist SENSe therapy centers have been set up to deliver SENSe therapy to stroke survivors across three states in Australia. The new specialist therapy centers are linked with healthcare networks and universities or research institutes. The SENSe therapy centers will permit delivery of therapy to stroke survivors living in the community. Therapy may be delivered at the center or in the client’s home.

Occupational therapists and physiotherapists skilled and credentialled in SENSe therapy will deliver SENSe therapy to stroke survivors across the specialist therapy centers, using a pragmatic, within-subject wait list design [42]. The wait list design will evaluate change in outcomes over a 6-week period of usual care not associated with SENSe therapy, compared to a 6-week period of SENSe therapy delivered by credentialled therapists. During the wait list phase, participants will receive usual care, which will be monitored. Upper-limb therapy will not be restricted for participants during the control wait list phase; rather, participants will receive ‘usual care’ conditions [44]. Consistent with an independent review and analysis of ‘usual care’ usually received in health services in Australia (based on national audit and knowledge-translation study), this will usually not involve specific sensory rehabilitation, such as SENSe therapy [44]. Participants may continue to receive usual care during the SENSe therapy intervention period. Our prior controlled clinical trials provide evidence that exposure to sensory stimuli alone and/or current usual care is not usually sufficient to affect clinically significant improvement in somatosensory function [34,36,37]. All services and usual care received will be monitored.

Stroke survivors attending specialist SENSe therapy centers will be assessed on four occasions: baseline (i.e., Assessment 1, A1); after 6 weeks of usual care (i.e., A2); after 6 weeks of SENSe therapy (i.e., A3); and at follow up, 12 weeks post A3 (i.e., A4). All participants attending SENSe therapy centers will receive SENSe therapy (10 sessions) over a 6-week period. Assessors for health outcomes of stroke survivors will be blinded to study design and timing of therapy delivery. Researchers and statisticians involved in the data analysis will also be blinded to study design and timing of therapy delivery.

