SENSe therapists will not be blinded due to pragmatic reasons. It is planned that each therapist will deliver SENSe therapy to up to 12 stroke survivors. A secondary analysis will permit investigation of the association between stroke survivor outcomes achieved and the therapist’s amount of experience in delivering SENSe therapy. The study is approved by Austin Human Research Ethics Committee (HREC/18/Austin/153), and all experiments will be performed in accordance with the Declaration of Helsinki. Site-specific ethics approvals were also obtained. All participants will give voluntary informed consent.

Sample size: Stroke survivors—The SENSe CONNECT study design requires a within-subject, repeated measures analysis. The within-group analysis from the original SENSe randomized controlled trial (RCT) revealed a Cohen d of 0.366 for the somatosensory function outcome (repeated measures, small group *n* = 22/50; [34]). To achieve a within-group effect of d = 0.366 for a power of 0.8, a minimum sample of *n* = 61 is required. In the current study, the proposed sample size of *n* = 72 to 192 (i.e., 18 to 48 deliveries at each of the 4 centers) achieves this minimum and allows for dropout or poor recruitment. Assuming the variability in changes found in the SENSe RCT is replicated in the delivery of SENSe therapy, a maximum sample size of *n* = 192 will have a high degree of precision for estimating the effect size obtained within the SENSe therapy centers. The larger sample size will also facilitate generalizability of effect estimates to the broader target population of survivors of stroke living in the community. Therapists—At each specialist SENSe therapy center, it is planned that 3 or 4 therapists will each deliver SENSe therapy to 6 to 12 stroke survivors (i.e., 18 to 48 deliveries at each site; 72 to 192 across sites). A sample of 12 to 16 therapists was chosen to maximize replication across upskilled therapists while exploring the association between the amount of experience in delivery of SENSe therapy and therapy outcomes.

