Effect of SENSe therapy: We will evaluate the therapeutic gain in arm somatosensory function for stroke survivors (primary outcome) during the SENSe therapy phase compared to that of the usual care phase by estimating the mean within-person difference between the two trends and the associated 95% confidence intervals. The magnitude of change in arm somatosensory function under the two conditions will be calculated as a standardized effect size and compared to the benchmark effect size obtained in the original SENSe RCT (comparable cohort) [34]. Statistical estimates of change will be reported with 95% confidence intervals, and the extent of overlap across studies in these estimates of change will be described. Confidence intervals for the difference between mean change scores from the present and benchmarked study [34] will also be obtained. The analysis design will include the SENSe therapy center as a variable, to evaluate its potential systematic effect. Individual participant characteristics that may impact magnitude of therapeutic gain, such as age and time post-stroke, will be explored. Improvement in secondary outcomes, i.e., clinician-rated performance in valued activities, arm use, and quality of life, will also be evaluated pre–post therapy. Depending on verification of the normal distribution assumption, either a t-distribution or a bootstrapping method will be used to obtain the confidence interval. Maintenance of the intervention effect will be evaluated at the 12-week follow up (A4).

Treatment fidelity and behavior change: High fidelity delivery will be defined as a score of 80% or higher on the SENSe treatment fidelity checklists [43]. Audit data from treatment sessions will be independently summarized for each SENSe therapy treatment program delivered. The number of therapy deliveries achieving high treatment fidelity will be summarized. Pre- and post-implementation questionnaires of therapist knowledge, confidence, and ability to deliver SENSe therapy will be summarized and response tendencies will be examined using contingency tables, McNemar’s test, and graphical representation.

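### Section 2.4 defines the stroke-survivor primary outcome as the uncontrolled pre–post SENSe change, and the sample size appears to match it, but the primary analysis in Section 2.8 is the difference between the SENSe-phase and usual-care-phase trends

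*Protocol article*

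**What the plan says.** Section 2.4 (Outcomes, Stroke survivors): "The primary outcome is change in arm somatosensory function, pre–post SENSe therapy, across three somatosensory domains". The index combines three somatosensory tests. The usual-care phase is not mentioned.

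Section 2.8 (Data Analysis, Effect of SENSe therapy) attaches the primary label to a comparison. It opens "We will evaluate the therapeutic gain in arm somatosensory function for stroke survivors (primary outcome" and goes on to specify the gain "during the SENSe therapy phase compared to that of the usual care phase by estimating the mean within-person difference between the two trends". The same paragraph plans to standardize the change under each of the two conditions and set it against the earlier RCT as a benchmark.

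Section 2.1.2 describes the comparison the design is built for: "The wait list design will evaluate change in outcomes over a 6-week period of usual care not associated with SENSe therapy", set against six weeks of SENSe therapy in the same people. Its sample size paragraph starts from a single standardized effect: "The within-group analysis from the original SENSe randomized controlled trial (RCT) revealed a Cohen d of 0.366 for the somatosensory function outcome". From this it derives a minimum of 61 and plans for 72 to 192.

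**The concern.** A3−A2 and (A3−A2)−(A2−A1) are different estimands with different variances. The first credits to SENSe everything that moves the index over those six weeks, including practice on repeated tests, recovery, and regression to the mean after selection on impairment. The second subtracts whatever the same people gained over six weeks of usual care.

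The order of phases is fixed and there is no randomized comparator, so the usual-care phase is the study's only internal control for time effects. Such effects cannot be dismissed. Section 2.2 admits new as well as chronic impairment with no limit on time since stroke, and Table 1 repeats the same three tests at all four assessments. An outcome definition that leaves out the usual-care phase gives up that control, and it gives a later report a textual basis for presenting the pre–post change as the primary result.

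**Working it through.** **1. The two quantities.** With assessments A1 (baseline), A2 (after usual care) and A3 (after SENSe):
- Section 2.4: A3−A2.
- Section 2.8: (A3−A2)−(A2−A1) = A3−2·A2+A1.

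**2. The plan's own sample size.** Inputs from Section 2.1.2 are d = 0.366 and power 0.8. Alpha is not stated; two-sided 0.05 is assumed, in line with the 95% confidence intervals in Section 2.8. For a paired t-test, power comes from the noncentral t with n−1 degrees of freedom and noncentrality d·√n. At n = 61, 0.366 × √61 = 2.859, the critical value is 2.000 and power is 0.803. The smallest n reaching 0.8 is 61, so the stated figure reproduces as the size for one within-person quantity with standardized mean 0.366.

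**3. Pre–post result with no SENSe benefit.** Assume the same drift δ in both phases, in SD of a six-week change. The documents give no value, so a range is used. The probability that the 95% interval for A3−A2 lies wholly above zero is the upper tail of the noncentral t with noncentrality δ·√n.

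| δ (SD) | δ·√72 | n = 72 | δ·√192 | n = 192 |
|---|---|---|---|---|
| 0.05 | 0.424 | 6% | 0.693 | 10% |
| 0.10 | 0.849 | 13% | 1.386 | 28% |
| 0.20 | 1.697 | 39% | 2.771 | 79% |
| 0.25 | 2.121 | 55% | 3.464 | 93% |

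Under the same assumption the contrast has mean δ−δ = 0, so its upper-tail error is 2.5% at either n. A larger study makes the pre–post error worse, because it estimates the drift more precisely.

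**4. Power for the contrast.** Let f = Var(contrast)/Var(single change), with visit variance σ² and between-visit correlation ρ.
- Equal correlation: Var(A3−A2) = 2σ²(1−ρ) and Var(A3−2·A2+A1) = 6σ²(1−ρ), so f = 3.
- AR(1): f = (6−8ρ+2ρ²)/(2−2ρ) = 3−ρ, which lies between 2 and 3 for positive ρ.

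If d = 0.366 describes a single six-week change and the usual-care change is zero, the standardized contrast is 0.366/√f.

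| f | d of contrast | n for 0.8 | power at 72 | power at 192 |
|---|---|---|---|---|
| 2 | 0.259 | 120 | 0.58 | 0.95 |
| 3 | 0.211 | 178 | 0.42 | 0.83 |

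A usual-care gain lowers these figures. With 0.1 SD, f = 3 gives (0.366−0.1)/√3 = 0.154, with power 0.25 at 72 and 0.56 at 192.

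**The case against.** The best defense is that Section 2.4 names the variable and the therapy window, while Section 2.8 names the comparison. Section 2.8 is the only place where the primary outcome is analyzed; it gives no stand-alone pre–post test of that outcome and keeps uncontrolled pre–post wording for the secondary outcomes. The wait-list design in Sections 2.1 and 2.1.2 and the incremental cost-effectiveness analysis against wait-list usual care agree with it. This stands as evidence of intent. A reader might infer that nothing indicates which quantity decides; the documents do not support that.

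Four further limits also stand.
- A reader might infer that the two definitions lead to opposite conclusions. What the working shows is a positive result beside a null one. A reversed sign would need the usual-care gain to exceed the SENSe gain.
- A reader might infer that the sample size certainly follows Section 2.4. The within-group wording suggests so, but n = 61 fits any within-person quantity with standardized mean 0.366, and the article does not say which change in the earlier RCT was standardized.
- Section 2.1.2 describes the comparison of phases but never calls it primary. Only Section 2.8 does.
- The drift values are assumptions. Section 2.1.2 says usual care is not usually enough for clinically significant improvement, which does not exclude small drift. At 0.05 SD the excess error is modest.

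Detail may properly be left to a fuller protocol or analysis plan. That does not answer this point, because the article itself gives two descriptions of one primary outcome.

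**Conclusion.** The mismatch is real and worth correcting. Section 2.4 defines an uncontrolled change, the sample size appears to be built on the same kind of quantity, and the stated primary analysis is a controlled contrast. The design points to the contrast as intended, so this is a definition and a sample size statement that were not brought into line with the analysis. The risk is conditional: it arises if the Section 2.4 definition is what gets reported as primary, and its size then depends on the unknown drift.

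The contrast's protection has limits too. It removes only a drift that is the same in both phases. If recovery slows over time, as could happen in people with new impairment, the contrast is biased against SENSe. The power figures rest on zero usual-care change, a variance ratio of 2 to 3, and d = 0.366 being a single-phase change. On those assumptions the upper planned sample supports the contrast and the lower one does not.

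**What to change.** 1. Section 2.4: define the stroke-survivor primary outcome as (A3−A2)−(A2−A1) on the normalized index, matching Section 2.8.
2. Sections 2.4 and 2.8: label the single-phase changes, A3−A2 and A2−A1, as supportive quantities, used for the benchmark against the earlier RCT under both conditions as already planned.
3. Section 2.1.2: state that 61 at power 0.8 applies to a single within-group change with d = 0.366, and restate the power or expected precision of 72 to 192 for the contrast, with the assumed variance ratio and usual-care change.

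No new data or visits are needed, since A1, A2 and A3 are already scheduled. The cost is a wider confidence interval for the primary result and a less favorable power statement, most visibly at the lower end of the planned range.

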### 2.5. Implementation Intervention

The current knowledge-translation study and implementation intervention developed by the research team are based on the Theoretical Domains Framework [14], and guided by strategies from the Behaviour Change Wheel [16] to facilitate practice change and Normalisation Process Theory [54] to enhance sustainability. Specifically, the multi-component implementation intervention to support knowledge translation includes (i) interactive training workshops, (ii) establishing a clinical lead and site champions; (iii) provision of educational materials and structured therapy booklets; and (iv) use of treatment fidelity checklists [43] to guide feedback on therapy and to assess outcomes.

Upskilling of therapists: Occupational therapists and physiotherapists will be upskilled in delivery of SENSe therapy by a trained clinical lead researcher from the central hub using multimedia resources. Training includes a 1.5-day interactive workshop, involving theory (1 h), practical hands-on SENSe training sessions (7 h), and applied treatment planning (2 h), and is supported by 3 independent learning modules that include supervised practice tasks and case scenarios (estimated to take 1 to 2 h each); the total time is approximately 13 to 16 h. Therapists are credentialed, via observation of a simulated therapy session at the end of the upskilling process. Participant therapists will also receive supervision and mentoring during delivery of SENSe therapy. This will be primarily via the treatment fidelity observations and audit feedback. Therapists are introduced to the treatment fidelity checklist [43] during upskilling sessions and encouraged to use it for self-evaluation. The treatment fidelity criterion checklist is also used by SENSe therapy trainers to provide feedback to therapists on treatment notes and observed therapy delivery.

### 2.6. SENSe Therapy Intervention

SENSe (Study of the Effectiveness of Neurorehabilitation on Sensation; [34]), is a science- and evidence-based rehabilitation therapy designed to help people with stroke regain a sense of touch and use it in daily activities (http://youtu.be/G9V3I30pn68; accessed on 2 October 2023). As such, the focus is on restoration of function rather than compensation. Clinical practice protocols and therapy tools [55] have been produced to facilitate implementation and quality delivery in clinical settings. The intervention will be delivered face to face by skilled and credentialled occupational therapists and/or physiotherapists within specialist SENSe therapy centers. SENSe therapy involves modules of sensory discrimination training of texture discrimination, sensing the position of the upper limb in space (proprioception), recognizing objects through the sense of touch, and learning how to apply these skills in daily tasks identified by the person with stroke (Figure 2). Seven training principles are used during the process of somatosensory discrimination training as follows: select; attentive exploration; feedback; calibrate; anticipate; repeat and progress; and transfer (http://youtu.be/G9V3I30pn68; accessed on 2 October 2023). Specially designed training tools are used and include grids and texture training wheels of surfaces with varying surface features, graded for large, medium, and fine surface differences; box-like apparatus and protractor scales for training wrist position sense; and graded sets of objects for functional tactile object recognition that train discrimination and recognition of object weight, crushability, shape, size, temperature, texture, and functional motion. The client selects two valued activities that they believe are impacted by their sensory loss to focus on in therapy. They are guided to discover the sensory challenges in the activity and how they can use their new skills to perform the task better. Examples include using a knife or fork, finding money in a wallet, doing up buttons, and using a remote-control device. The intervention will be tailored according to the level of impairment and functional goals of the stroke participant. The dose is 10 1-hour sessions, over a period of 6 weeks. The frequency of sessions is approximately twice a week. The number, duration, and specific content of all sessions are monitored using customized training forms.

